### Intervention

Participants in both groups will receive physical exercise and neuromuscular electrical stimulation after discharging form hospital. Physical exercise will be conducted for 2 hours per day following the principle of the Bobath concept, including posture control, passive movement, overturning movement, and bridge movement. Neuromuscular electrical stimulation will be conducted by using a portable muscle electricity biofeedback instrument (MyoNet-COW; NCC Electronic Co. Ltd, Shanghai, China) for 30 minutes per day. Both physical exercise and neuromuscular electrical stimulation will be carried out by trained therapists following the standard operation procedure guidance.

### Tele-supervising rehabilitation group

Under the guidance of trained therapists and with the help of caregivers, participants in the tele-supervising rehabilitation group will receive rehabilitation therapy at their home via using a telerehabilitation system (Figure 2). The telerehabilitation system consists of three parts: a doctor work platform, a patient platform and a proprietary network system. The network system provides sufficient bandwidth for remote diagnosis, treatment and data collection. The doctor work platform is composed of a high-quality video/audio system, electronic medical records system and remote control system. Therapists can obtain the medical history information from electronic medical records, guide the participants to do the physical exercise and neuromuscular electrical stimulation by the high-quality video/audio system, and collect data by the remote control system during rehabilitation therapy. The patient platform will be implemented at participants’ homes after randomization allocation, which includes the high-quality video/audio system, physiological data collection system and muscle electricity biofeedback instrument. Participants or their caregivers will receive rehabilitation guidance from therapists via the high-quality video/audio system. Electricity biofeedback instrument will provide neuromuscular electrical simulation to the participants and collect surface electromyography (sEMG). Physiological data collection system (NTH-M6; NCC Electronic Co. Ltd, Shanghai, China) will record body temperature, respiratory rate, pulse rate, blood pressure, surface electrocardiogram, and peripheral blood oxygen saturation during the process of therapy. These physiological data will be feedback to the doctor platform for supervision by the therapists. Each participant will receive rehabilitation therapy once per day.

**Figure 2 Fig2:**
[figure not shown]
**Schematic diagram of home-based tele-supervising rehabilitation.**

### Conventional rehabilitation group

Participants in the conventional rehabilitation group will receive rehabilitation therapy once per day in the outpatient department of Shanghai Number 5 Hospital, Fudan University. The therapeutic strategy is the same as the tele-supervising rehabilitation group except for using the telerehabilitation system. Physical exercise and neuromuscular electrical stimulation will be carried out face-to-face by a trained therapist at the bedside. Besides, the equipment model of the muscle electricity biofeedback instrument and physiological data collect system are the same as used in the tele-supervising rehabilitation group.

### Data measurement

Data measurement will be carried out by trained independent assessors, who are blinded to allocation and intervention, and who will be required to be prevented from learning allocation or intervention information from patients during outcome measurements. Baseline data assessment will be carried out in hospital before randomization allocation. In order to keep allocation and intervention from assessors, outcome measurements will be conducted at the neurology outpatient department at the end of intervention and 90-day follow-up. A specified trial staff member will make an appointment with patients the day before outcome measurements and will make suggestion about the next day’s physical examination including not to provide treatment information to the physician.

### Baseline assessment

Baseline assessment consists of epidemiologic data (including age, gender, history of present complaint, past medical history, physical examination, and auxiliary examination); NIHSS score, Barthel index score, mRS score, water swallow test, and sEMG. Meanwhile, physiological data will also be measured, which includes body temperature, respiratory rate, pulse rate, blood pressure, surface electrocardiogram, and peripheral blood oxygen saturation.

### Primary outcome measurement

Primary outcome measurement will be conducted by using the Barthel index at the end of intervention and 90-day follow-up. The Barthel index consists of ten items: presence or absence of fecal incontinence, presence or absence of urinary incontinence, help needed with grooming, toilet use, feeding, transfers, walking, climbing stairs, bathing and dressing. The score ranges from 0 to 100, with high scores demonstrating high activities of daily living [22,23].

### Secondary outcome measurement

Secondary outcome measurement, which includes NIHSS score, mRS score, 3-oz water swallow test and sEMG, will be carried out at the same time with the primary outcome measurement.

Neurological function deficient will be measured by NIHSS score; it has been confirmed as a widely used scale with high reliability and good convergent validity. NIHSS includes 11 items, ranging from 0 to 42, with low scores depicting good neurological function [24,25].

General disability condition will be measured by mRS score, which consists of 6 ranks: rank 0 demonstrates no disability symptoms; rank 1 demonstrates no significant disability, despite with symptoms, able to perform all usual duties and activities; rank 2 demonstrates slight disability, although with the ability to look after own affairs without assistance, but be unable to carry out all previous activities; rank 3 means moderate disability, requiring some help in daily life, but with the ability to walk without assistance; rank 4 means moderately severe disability, with the inability to walk without assistance and attend to own bodily needs without assistance; rank 5 means severe disability, depicts patients who are bedridden, incontinent or require constant nursing care; rank 6 equates to death [26,27].

Swallowing function and the presence of dysphagia will be measured by the 3-oz water swallow test [28]. Participants will be asked to drink 3 oz of warm water without interruption. Criteria for assessment of swallowing includes being unable to complete the task, coughing, choking, or with a wet-hoarse vocal quality exhibited either during or within 1 minute of test completion. Compared with other bedside assessment, the 3-oz water swallow test has high specificity and sensitivity in detecting aspiration in dysphagia patients after stroke [29].

As motor unit recruitment is crucial for evaluating muscle activity after brain infarction, sEMG will be employed to monitor the root mean-squared (RMS) value of target body regions. RMS value of the sEMG signals reflects the association of muscle activity with motor unit recruitment [30].

### Adverse events

Although therapeutic treatment will be conducted with the guidance of trained therapists, and the intervention strategy of the study is low risk, it is impossible to ignore adverse event measurement. Therefore, all the participants as well as their caregivers and research team staff will be asked to report adverse events. Besides, physiological data will be recorded to assess the physical condition of the participants during intervention. A group of research staff will be trained to record and analyze physiological data and deal with adverse events. If severe adverse events happen, the group will report the events to the study director and quality control committee and the study will be suspended if necessary. Once the study has to be suspended because of severe adverse events, only when the severe adverse events can be successfully prevented, can the suspended study be recommenced.

### Quality control

The study has been registered in the Chinese Clinical Trial Registry (ChiCTR) and supervised by the superior authority. A Quality Control Committee will be established before trial initiation, and will consist of six members, including two neurologists, two rehabilitation specialties, and two statisticians. The committee will help the research team write the trial protocol and standard operation procedure, supervise the whole process of the study, and control the quality. The research team will receive specific training for standardizing the procedure of the entire study including participant recruitment, therapeutic intervention, outcome measurement and data analysis. Additionally, all the data should be checked according to the standard operation procedure of the study at least once per week during the study process.

### Statistics

An independent statistician, who is blind to allocation and intervention, will take charge of data analysis. All the variables will be analyzed according to an intent-to-treat (ITT) basis, and the statistical tests will be 2-side and at the 5% significance level. All the participants under randomization will be included in the analysis, regardless of whether or not they adhered to the treatment or provided complete data sets. For providing valid inferences with less restrictive assumptions, multiple imputation will be performed to analyze missing data. Continuous variables will be summarized by means and standard deviation. The normality of the distribution will be checked before comparison by using the Shapiro-Wilk test. Normally distributed variables will be compared by using the *t*-test, and the Mann-Whitney *U-*test will be performed to compare non-normally distributed variables. Discrete variables will be summarized by relative frequencies and analyzed by using a non-parametric test. The level of statistical significance will be set at *P* < 0.05. SAS V9.1 (SAS Institute, Cary, NC, USA) will be employed for all the statistical analysis. The statistical analysis plan will be fully specified and approved before unmasking.

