### Sample measurement

Primary outcome of the study will be measured by using the Barthel index. The main purpose of the study is to investigate the efficacy of tele-supervising rehabilitation compared with conventional rehabilitation, and sample size calculation will be conducted by following formula:$$ {n}_1={n}_2=\frac{2{\left({z}_{a/2}+{z}_{\beta}\right)}^2{\sigma}^2}{{\left({\mu}_1-{\mu}_1\right)}^2} $$

According to the previous study, difference in means of 90-day post-stroke Barthel index is 7.8 and standard deviation is 18.35 [21]. Taking 5% 2-side significance level and 80% power into consideration, at least 87 participants need to be recruited in each group. For 20% attrition, our study will recruit 105 participants in each group.

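### A Shapiro-Wilk pre-test on the trial data picks the primary test for the Barthel index, and one of its two branches does not test the mean difference on which the trial is sized

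*Protocol article*

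**What the plan says.** Four statements in the protocol article bear on this.

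- **Outcome** (Primary outcome measurement): "Primary outcome measurement will be conducted by using the Barthel index at the end of intervention and 90-day follow-up". Table 1 puts these visits at 90 and 180 days after the intervention starts. Of the ten-item index it says "The score ranges from 0 to 100".
- **Sizing** (Sample measurement): the two-means formula is used with the inputs "difference in means of 90-day post-stroke Barthel index is 7.8 and standard deviation is 18.35". The result is "Taking 5% 2-side significance level and 80% power into consideration, at least 87 participants need to be recruited in each group", followed by "For 20% attrition, our study will recruit 105 participants in each group".
- **Choice of test** (Statistics): "The normality of the distribution will be checked before comparison by using the Shapiro-Wilk test". Variables judged normal are compared by the t-test, the others by the Mann-Whitney U-test. Discrete variables go straight to a non-parametric test. Continuous variables are summarised by mean and standard deviation whichever test is used.
- **Missing data** (Statistics): everyone randomised is analysed, and "multiple imputation will be performed to analyze missing data".

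The same section says that the SAP will be completed and approved before unmasking.

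**The concern.** The protocol names no single test for its primary outcome. A significance test on the outcome data selects it, and the two candidates answer different questions. The t-test addresses the difference in mean Barthel index, which is what the trial is powered for. The Mann-Whitney test addresses whether scores in one arm tend to exceed those in the other. Because means and standard deviations are reported in either case, the p-value and the summary beside it could concern different quantities.

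The rule also leaves room for more than one answer:

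- The index is primary at two visits, so the gate could choose the t-test at one and Mann-Whitney at the other.
- The text does not say whether normality is checked per arm or pooled, or on which data set once missing values are imputed. Completed sets can fall on different sides of the gate.
- It does not say whether a stepped 0 to 100 score counts as continuous, and so meets the gate, or as discrete, and so bypasses it.

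What is at stake is whether the primary result, and the quantity it estimates, are defined before the data are seen.

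**Working it through.** **1. The plan's own figure.** Inputs from Sample measurement: difference 7.8, SD 18.35, two-sided 5%, power 80%.

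n per group = 2 × (1.960 + 0.842)² × 18.35² / 7.8² = 86.88, rounded up to 87. This reproduces the protocol, so the sizing rests on a comparison of means.

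**2. How often would the gate send the Barthel index to Mann-Whitney?** The protocol gives no mean, shape or ceiling proportion, so these are assumptions: normal scores rounded to steps of 5, capped at 0 and 100, with SD 18.35 after capping in the control arm, and control means from 50 to 85. There were 87 per arm and 2,000 simulated trials per cell, with Shapiro-Wilk at 5%. Per arm means that the gate fails if either arm rejects. The effect columns add 7.8 points to the treated mean.

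| Control mean | At ceiling | Per arm, no effect | Pooled, no effect | Per arm, effect 7.8 | Pooled, effect 7.8 |
|---|---|---|---|---|---|
| 50 | 0.5% | 21% | 28% | 22% | 29% |
| 60 | 2.2% | 25% | 53% | 56% | 89% |
| 70 | 8.2% | 95% | 100% | 100% | 100% |
| 75 | 14.8% | 100% | 100% | 100% | 100% |
| 80 | 25.8% | 100% | 100% | 100% | 100% |
| 85 | 42.5% | 100% | 100% | 100% | 100% |

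With 105 per arm, the size of a completed data set after imputation, the per-arm rates without an effect are about 25% at mean 50, about 35% at mean 60 and 99% or more from 70 upwards.

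**3. Does the two-stage rule damage the error rates?** Same simulation, pooled gate:

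| Control mean | Type I: two-stage / t-test alone | Power: two-stage / t-test alone |
|---|---|---|
| 50 | 4.6% / 4.4% | 79.6% / 80.3% |
| 60 | 4.6% / 4.8% | 79.5% / 81.6% |
| 70 | 5.6% / 5.4% | 79.8% / 81.4% |
| 75 | 6.3% / 6.0% | 82.4% / 83.3% |
| 80 | 4.8% / 4.8% | 86.0% / 85.6% |
| 85 | 5.2% / 4.9% | 91.3% / 90.1% |

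The simulation standard error is √(0.05 × 0.95 / 2000) = 0.5 percentage points for type I error and √(0.8 × 0.2 / 2000) = 0.9 points for power. The rule follows the t-test to within 0.3 points on type I error, and its largest power deficit is 81.6 − 79.5 = 2.1 points. With 105 per arm and the per-arm gate, type I error was about 4 to 5.5%.

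**4. What happens across imputed data sets?** Assumptions: 105 per arm, 20% missing (84 observed and 21 imputed), 20 imputations from a normal model capped at 0 and 100, Shapiro-Wilk on each completed pooled set, 400 simulated trials. The means and SDs below are those before rounding and capping.

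| Mean, SD | Trials in which the sets disagree on the test |
|---|---|
| 50, 18.35 | 54% |
| 62, 19 | 69% |
| 78, 22 | 0% (all sets choose Mann-Whitney) |
| 90, 28 | 0% (all sets choose Mann-Whitney) |

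In the middle of the scale the written rule often yields no single test. Near the ceiling it yields one, but not the one used for sizing.

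**The case against.** The strongest reply is that little is lost in practice. Error rates are close to those of the t-test, means and SDs are reported anyway, and a fuller SAP is promised. The point on error rates stands in full. The appeal to the SAP stands only in part: combining rules may be left to it, but the normality gate is written into the protocol, and an SAP that follows the protocol inherits it.

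A reader might infer four stronger things that the documents do not support:

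- **That the result cannot be pooled after multiple imputation.** The protocol names neither Rubin's rules nor a quantity to pool, so nothing it states is impossible. A U-test p-value does not fit Rubin's rules, but a rank-based estimate with a standard error, such as the probability of superiority, can be pooled.
- **That the primary analysis will probably be Mann-Whitney.** This depends on a Barthel distribution that the protocol does not give. Under the assumptions above, the chance runs from about one in five to certainty.
- **That the two-stage rule inflates false positives or costs power.** The simulation shows neither to a material degree.
- **That the rank branch leaves no mean difference or interval to report.** A mean difference follows from the reported summaries, and a Hodges-Lehmann shift with a confidence interval can accompany the test. The narrower point is that the p-value would not test that mean difference.

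**Conclusion.** The concern holds in a limited form. The protocol lets a normality test on the trial data choose the primary test. The choice may differ between the two primary time points or between imputed sets, and under the rank branch it leaves the mean difference of 7.8 (SD 18.35) on which the trial is sized. How the gate operates on imputed data, and what would be pooled on the rank branch, are not stated.

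The gate and its mismatch with the sizing are plain from the text. The frequency of switching is conditional on assumed capped scores in 5-point steps: with no effect and a per-arm check, about 20 to 35% at means of 50 to 60, higher if pooled, and near certainty from about 70. The harm is to the definition of the estimand and the primary result, not to type I error or power. It should be corrected, but it does not undermine the design: with a comparison of means fixed in advance, the calculated 87 per group stands.

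**What to change.** Delete the normality gate. Pre-specify one comparison of mean Barthel index, adjusted for baseline Barthel (already collected) and the two stratification factors, age group and NIHSS group. Apply it at each primary time point that the protocol names; this change need not, and should not silently, drop one of them. Fit the model in each imputed data set, pool by Rubin's rules, and report the mean difference with its 95% confidence interval. With 87 or more per arm, such a comparison does not need normally distributed raw scores.

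Keep a rank-based or ordinal analysis as a pre-specified sensitivity analysis, and state the quantity to be pooled for it. For the other continuous outcomes, fix the method by type of variable, not by a pre-test.

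The cost is wording: the Statistics section of the protocol must be amended as well as the SAP, before unmasking. No extra data or participants are needed. The downside is that a mean difference is reported even when scores are skewed, which the sensitivity analysis covers.

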### Ethics

The HTRBIP trial follows the Helsinki Declaration and has been approved by the Independence Ethics Committee of the Fifth Peoples’ Hospital of Shanghai, Fudan University (ethic approval number: 2014-ETRE-066). Participants will be acquainted with informed consent and asked to sign for it before being recruited.

### Dissemination policy

The HTRBIP trial study and results will be published in peer-reviewed journals in line with the reporting guidelines; namely, TIDieR for description of interventions and the Consolidated Standards of Reporting Trials (CONSORT) extension for non-pharmacological drugs. Trial results will be submitted to the trial registry, and will be communicated to participants via written and oral reports. The results will also be reported to local policy-makers (Shanghai Municipal Commission of Economy and Informatization, Shanghai Municipal Commission of Health and Family Planning). Additional stakeholders, including telerehabilitation device manufacturers and network service corporations, will be informed of the trial findings. Trial results will be disseminated regardless of the magnitude or direction of effect.

## Discussion

Stroke is the leading cause of adult death and disability in China, and brain infarction is its majority component. Since over 50% of brain infarction patients are still suffering from physical disabilities after discharge from hospital [20], and because most brain infarction survivors in China used to conduct rehabilitation at home, a novel rehabilitation strategy is needed to facilitate rehabilitation in patients’ residences under professional supervision.

Home-based telerehabilitation, which utilizes information and communication technology to connect patients and therapists, is considered as a potential solution for poor rehabilitation outcome of brain infarction patients after discharging from hospital [31,32]. Some research groups conduct clinical trials to investigate the feasibility of home-based physical rehabilitation. To date, there are ten RCTs investigating post-stroke telerehabilitation [20]. However, because of small sample size, significant heterogeneity and high risk bias; these previous RCTs could not conclude the practical guidance for post-stroke telerehabilitation application; thus, more adequately powered studies are required. Additionally, because there are currently no clinical trials evaluating the effectiveness of telerehabilitation for brain infarction patients worldwide, it is reasonable for us to conduct this clinical trial to provide new evidence for home-based tele-supervising rehabilitation application.

The HTRBIP trial is designed as an assessor blinded, paralleled RCT. Tele-supervising rehabilitation will be conducted through a specialized system that can connect therapist and patient over distance; data collecting will be simultaneously performed during rehabilitation. Barthel index at the end of intervention and at 90-day follow-up will be evaluated as primary outcome measurement, which represents the general physical function for disabled patients after brain infarction. NIHSS score, mRS score, 3-oz water swallow test and sEMG will be employed for secondary outcome measurement. Furthermore, adverse events will be recorded for safety evaluation. For tele-supervising rehabilitation specialized remote interaction devices are required, and because it is impossible to blind the intervention strategy to the patients and therapists, this trial could not be double-blinded. To make up for this limitation and ensure the quality of the trial, outcome assessors and data statisticians will be blind to the allocation and intervention strategy.

The HTRBIP trial will evaluate efficacy and safety of home-based tele-supervising rehabilitation for brain infarction survivors in China, which is expected to supplement evidence for telerehabilitation application, and increase the experience gained for its practice.

